## Abstract

Premenstrual syndrome (PMS) is a widespread and under-recognized disorder, characterized by cyclical recurrence of physical, psychological, and behavioral symptoms during the luteal phase, significantly impacting the daily functioning of women. Cognitive Behavioral Therapy (CBT) is an established non-pharmacological strategy for PMS, while *Brahmi* (Bacopa monnieri), a classical Ayurvedic herb, has traditionally been used to enhance cognition, reduce anxiety, and support emotional balance. This exploratory study evaluates whether combining *Brahmi* with CBT offers additional benefit compared to CBT alone. It is a double-blind, randomized, placebo-controlled exploratory clinical trial (CTRI/2025/02/081239) conducted at the Amrita School of Ayurveda, Kollam, Kerala, with sponsorship from the Central Council for Research in Ayurveda Sciences (CCRAS). Forty-six women aged 18–24 years, diagnosed with moderate to severe PMS using the Premenstrual Symptoms Screening Tool (PSST) and the Daily Record of Severity of Problems (DRSP), will be recruited and randomly assigned to receive either CBT with *Brahmi* tablets or CBT with placebo tablets. The primary outcomes include reduction in PMS severity, assessed by DRSP, and improvement in quality of life measured with the Quality of Life Enjoyment and Satisfaction Questionnaire (Q-LES-Q SF). Secondary outcome is reduction in functional disability measured using the Sheehan Disability Scale. Assessments will be conducted at baseline, during treatment, and at follow-up. Statistical analysis will be carried out using repeated measures ANOVA with Bonferroni-adjusted post hoc tests, significance set at *p* < 0.05, and effect sizes reported. A limitation of this design is that it cannot disentangle the individual effects of *Brahmi* from CBT, allowing conclusions only on the combined intervention. The study aims to generate preliminary exploratory evidence for a safe, integrative, and accessible approach to PMS management in young women.

## 1 Introduction

### 1.1 Background

According to the American College of Obstetricians and Gynacologists (ACOG), many women experience physical and emotional changes in the days preceding menstruation. When these symptoms occur cyclically and significantly interfere with a woman’s normal life, they are classified as Premenstrual Syndrome (PMS) (1). In India, reported prevalence estimates of PMS vary widely, ranging from 14.3% to 74.4% (2). Aside from mild forms, PMS can lead to significant disruptions in daily life, contributing to emotional distress, interpersonal challenges, sexual dysfunction, and a range of physical and psychological health problems (3).

If left untreated, PMS can develop into Pre-Menstrual Dysphoric Disorder (PMDD), a more severe psychiatric condition characterized by extreme mood changes, irritability, and functional impairment, including suicidal ideation. PMDD is recognized as a depressive disorder in the DSM-5 (Diagnostic and Statistical Manual of Mental Disorders, 5th Edition) with a prevalence of 3%–8% (4). It is recognized in the International Classification of Diseases (ICD), listed in ICD-10 as “Premenstrual Tension Syndrome” (N94.3) and in ICD-11 as “Premenstrual Dysphoric Disorder” (5), highlighting it as a distinct and clinically significant entity, separate from PMS. Its diagnosis requires symptom tracking over two consecutive menstrual cycles. Therefore, early identification and effective intervention for PMS are critical to prevent progression to PMDD.

### 1.2 Literature review

A comprehensive literature review was undertaken to explore both modern and Ayurvedic perspectives on Premenstrual Syndrome (PMS) and the potential role of *Brahmi* (Bacopa monnieri). Electronic databases including PubMed, ScienceDirect, and Web of Science were searched using keywords such as *“Premenstrual Syndrome,” “Cognitive Behavioral Therapy,” “Ayurveda,” “Bacopa monnieri,” “Integrative medicine,”and “Clincal Trial*.” Classical Ayurvedic texts (*Charaka Samhita, Sushruta Samhita, Ashtanga Hridaya)* were reviewed for symptomatology analogous to PMS and descriptions of *Brahmi*. Relevant studies, clinical trials, and reviews published in English were included, with emphasis on those addressing psychological, and neuroendocrine aspects. References were selected based on their scientific relevance and credibility to ensure a holistic understanding of the topic.

The management of Premenstrual Syndrome (PMS) often requires a multimodal approach, encompassing pharmacological options such as combined oral contraceptives and selective serotonin reuptake inhibitors, along with non-pharmacological strategies including psychological interventions and lifestyle modifications (3). Cognitive Behavioral Therapy (CBT), in particular, is a structured, evidence-based intervention designed to help individuals recognize and modify maladaptive thoughts and behaviors (3). Evidence suggests that CBT can be beneficial in alleviating the emotional and psychological symptoms associated with PMS, thereby contributing to improved quality of life (6, 7).

While there is no direct reference to PMS in classical Ayurvedic texts, symptoms closely resembling PMS have been described under various functional imbalances. Traditional Ayurvedic scholars recognized that physical illnesses can affect mental health and vice versa—an idea consistent with modern psychosomatic medicine (8). Symptoms of *Vata* vitiation—*the principle governing movement and nervous system functions*—include muscle stiffness, headache, fatigue, body ache, insomnia, and sadness (9). *Pitta*—*the principle of metabolism, heat, and transformation*—when aggravated, manifests as anger and confusion (10). *Kapha*—*the principle of structure, stability, and fluid balance*—in excess produces lethargy, excessive sleep, and nausea (11). *Udāvarta*, a pathological state attributed to the obstruction or reverse flow of *Vata*, particularly from suppression of natural urges, presents with abdominal distension, bloating, constipation, heaviness, emotional instability, and mental disturbances (12). These descriptions correspond closely to the symptomatology of PMS. Furthermore, in more severe cases like PMDD, additional symptoms of abdominal distention and cramps (13), emotional agitation, crying spells, and abnormal behavior have also been described (14). In Ayurveda, *Unmada* is described as a spectrum of mental disturbances characterized by disorganized thought, emotional dysregulation, and impaired social functioning, which further parallels the severe psychological presentations of PMDD.

### 1.3 Ayurvedic perspective

In Ayurveda, *Brahmi* (Bacopa monnieri) is regarded as a *Medhya Rasayana*, a rejuvenating herb for the mind and nervous system. Classical texts describe it as a tonic that nurtures memory, reduces stress, and promotes emotional balance. It has long been used to calm the mind and strengthen mental resilience, qualities that are particularly relevant when addressing the emotional fluctuations seen in PMS (15).

### 1.4 Modern pharmacological perspective

Modern research supports these traditional insights by showing that *Brahmi* acts on several important brain chemicals, including serotonin, dopamine, Gamma-Aminobutyric Acid (GABA), and acetylcholine—all of which are linked to mood regulation and PMS (16, 17). It also contains natural compounds like flavonoids and saponins that protect the brain from oxidative stress, reduce inflammation, and improve communication between nerve cells. These effects are thought to work through multiple pathways, such as cholinergic (18), dopaminergic (19), serotonergic (20), and GABAergic systems (18).

Interestingly, *Brahmi* also benefits gut health. Since most of the body’s serotonin is produced in the gut, disturbances there can affect both mood and inflammation. With its prebiotic properties, *Brahmi* helps restore a healthier gut environment, supporting the gut–brain connection and contributing to emotional stability (21, 22).

Together, these traditional and modern perspectives suggest that *Brahmi* may play an important role as a supportive therapy for PMS, especially in easing mood-related and neuroendocrine symptoms.

### 1.5 Need for the trial

Premenstrual Syndrome (PMS), if unaddressed, may progress to Premenstrual Dysphoric Disorder (PMDD), affecting mental health and daily life. Early diagnosis and timely care are vital. This trial explores whether combining Cognitive Behavioral Therapy (CBT) with oral *Brahmi* (Bacopa monnieri) tablets offers added benefit over CBT alone in managing moderate to severe PMS.

### 1.6 Research hypothesis

This exploratory study hypothesizes that combining Cognitive Behavioral Therapy (CBT) with oral intake of *Brahmi* (Bacopa monnieri) 500 mg once daily for two menstrual cycles may offer additional improvement in Premenstrual Syndrome (PMS) symptoms compared to CBT alone, based on Brahmi’s potential neurocognitive, emotional, and gut-brain modulatory properties.

## 2 Study objectives

### 2.1 Outcome measures

#### 2.1.1 Exploratory primary objectives

To explore the potential effect of Cognitive Behavioral Therapy (CBT) with versus without oral administration of 500 mg Brahmi tablet once daily on the severity of premenstrual symptoms, as assessed by the Daily Record of Severity of Problems (DRSP) (23).To explore the impact of the intervention on quality of life, as assessed using the Quality-of-Life Enjoyment and Satisfaction Questionnaire Short Form (Q-LES-Q SF 12) (24).

#### 2.1.2 Exploratory secondary objective

To explore the effect of the intervention on functional impairment during PMS-related menstruation, as assessed by the Sheehan Disability Scale (SDS) (25).

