## 4 Outcome measures

### 4.1 Exploratory primary outcomes

• Changes in PMS symptom severity, as measured by the Daily Record of Severity of Problems (DRSP) across two intervention cycles.

• Changes in quality of life, as assessed by the Quality-of-Life Enjoyment and Satisfaction Questionnaire Short Form (Q-LES-Q SF 12) from baseline to post-intervention.

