### 4.2 Exploratory secondary outcomes

• Changes in functional impairment, as measured by the Sheehan Disability Scale (SDS) total and domain-specific scores, reflecting work, social, and family functioning.

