#### 4.6.4 Interventional phase

During Cycle 3 and Cycle 4, participants will continue to maintain the DRSP daily from Day 1 to the end of each cycle. Additionally, Sheehan Disability Scale (SDS) and Quality of Life Enjoyment and Satisfaction Questionnaire Short Form (Q-LES-Q-SF) will be assessed on Day 1 or 2 of each cycle using retrospective recall. All scores will be recorded in Microsoft Excel. Assessments will be done using paper-pencil in English.

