Interventional phase	Sheehan Disability Scale (SDS), Q-LES-Q-SF	Day 1 or 2 of each cycle (retrospective recall)	Paper-pencil	English	Cycle 3 and Cycle 4, retrospective assessment of previous cycle	Scores recorded in Microsoft Excel
Documentation	Informed Consent Form (ICF), Patient Information Sheet (PIS)	Before enrollment	Paper	English & Malayalam	Baseline, before Cycle 1	Digital log maintained

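### The SDS, the only secondary outcome, is given inconsistent rating windows, and neither stated window isolates the premenstrual days

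*Protocol article*

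**What the plan says.** The condition is defined by phase. The Abstract describes PMS as "cyclical recurrence of physical, psychological, and behavioral symptoms during the luteal phase", and Section 1.1 speaks of "physical and emotional changes in the days preceding menstruation".

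The SDS objective in Section 2.1.2 names a different phase: "To explore the effect of the intervention on functional impairment during PMS-related menstruation". The matching outcome in Section 4.2 names none: "Changes in functional impairment, as measured by the Sheehan Disability Scale (SDS) total and domain-specific scores".

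Section 4.6.4 says the SDS and the Q-LES-Q-SF "will be assessed on Day 1 or 2 of each cycle using retrospective recall". The SDS and Q-LES-Q-SF row of Table 2 (Section 4.6.5) gives the window as "retrospective assessment of previous cycle", again without a phase.

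Section 3.4 states that oral medication is withheld in both groups during menstrual bleeding. For the Q-LES-Q-SF, one of two primary outcomes, Section 4.1 names no phase: "Changes in quality of life, as assessed by the Quality-of-Life Enjoyment and Satisfaction Questionnaire Short Form (Q-LES-Q SF 12) from baseline to post-intervention".

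**The concern.** Women enter this trial because of a phase-limited disorder, and the SDS is its only secondary outcome. Three windows bear on that outcome: luteal (the condition), menstrual (the objective) and the previous cycle (the form). The two written for the SDS disagree with each other, and neither is the premenstrual phase.

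The window decides what participants are asked to rate, so later analysis cannot recover it. If participants rate a cycle as a whole, an effect on premenstrual functioning may be mixed with days on which no PMS symptoms are expected. A small SDS difference would then be hard to interpret, because it could mean no premenstrual effect or a diluted one. The trial is meant to find signals and to report effect sizes (Sections 3.1 and 4.7), so this affects its main output.

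**Working it through.** The plan gives no figure for the recall window, so the check is mainly textual.

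**Step 1. The windows side by side.**

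| Source | What it fixes | Window |
|---|---|---|
| Abstract, Section 1.1 | the condition | luteal phase, before menstruation |
| Section 2.1.2 | SDS objective | menstruation |
| Section 4.2 | SDS outcome | no phase named |
| Section 4.6.4 | SDS administration | Day 1 or 2, by recall |
| Table 2 | SDS recall period | previous cycle, no phase named |

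**Step 2. Can the form measure the objective as worded?** On Day 1 or 2 the current bleeding has only begun. The bleeding that opened the previous cycle began one cycle length earlier, which is 25 to 35 days under Section 3.3.1. A Day 1–2 recall of the previous cycle is therefore poorly placed to measure impairment during menstruation.

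**Step 3. The objective against the tablet schedule.** Under Section 3.4 neither arm takes tablets during bleeding. Read literally, the objective asks about the days on which no study tablet is taken. This mismatch should be reconciled in the wording of the objective. It says nothing about the dosing schedule itself.

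**Step 4. Illustration of dilution.** Inputs:
- cycle length *L* = 25 to 35 days (Section 3.3.1)
- symptomatic days *s* = 7 to 14, an assumption, because the documents give no number

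Further assumptions: the recalled score behaves like an equal-weight average over all days, and the whole effect falls on symptomatic days.

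Share of the raw premenstrual effect retained = *s* / *L*; symptom-free share = 1 − *s* / *L*.

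| *s* | *L* | Retained | Symptom-free |
|---|---|---|---|
| 7 | 35 | 7/35 = 20% | 80% |
| 7 | 28 | 7/28 = 25% | 75% |
| 14 | 28 | 14/28 = 50% | 50% |
| 14 | 25 | 14/25 = 56% | 44% |

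**Step 5. No conversion to power.** The sample size in Section 4.2.2 reproduces: 2 × 2.85 × (1.96 + 1.28)² / 1.83² = 17.87, rounded up to 18 per group; 18 / 0.8 = 22.5, rounded up to 23; 46 in total. It is not in dispute. The section does not name the scale behind 1.83 and 2.85, so those values cannot be used to express SDS dilution as lost power.

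**The case against.** The case on the other side has several parts.

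- **Table 2 may only identify which cycle the form refers to.** The entry sits in a timeline column, and the instruction printed on the form may be in the full protocol. This is fair: the article does not say that every day is weighted equally. But where the article does name an SDS window, it gives two that disagree.
- **Averaging is an inference.** The SDS is a recalled rating made just after the premenstrual days, so recall may lean towards them. This stands. The stated window leaves that weighting to each participant.
- **The illustration scales only the raw effect.** If scores really averaged over days and most between-woman variation arose on symptomatic days, the standard deviation would shrink too, and the standardized effect might change little. This stands, so 20% to 56% is not a measure of lost signal.
- **The menstruation wording may be loose English for PMS.** That is plausible, since the DRSP objective in Section 2.1.1 refers to premenstrual symptoms. It would still need correcting, and the only window left would be the unrestricted previous cycle.
- **The trial is exploratory and the daily DRSP is untouched.** Both are true. They limit the consequence but do not make the SDS windows agree.

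A reader might go further and infer that the Q-LES-Q-SF has the same error. The documents do not support that. Sections 2.1.1 and 4.1 target quality of life without a phase, so a cycle-level rating is consistent with them. Tablets outside bleeding and therapy sessions on days 5, 12, 19 and 26 also do not confine benefit to luteal days.

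**Conclusion.** The point holds for the SDS. The objective, the recall window and the definition of the condition do not agree, and neither stated SDS window isolates the premenstrual days. Followed as written, the plan would not measure its stated secondary objective, and the form may dilute a premenstrual effect on function. This is more than a clerical matter, because it changes what the only secondary outcome measures.

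The size of any dilution cannot be derived from the documents. The 20% to 56% range depends wholly on the assumed 7 to 14 symptomatic days, equal weighting of days and an effect confined to symptomatic days.

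Two stronger readings should be avoided. One is that the rating covers mostly symptom-free days: with 14 symptomatic days this fails in a 25-day cycle (44% symptom-free) and is exactly half in a 28-day cycle. The other is that a null SDS result would be uninterpretable: it would be hard to interpret, in a trial whose daily symptom diary is unaffected. For the Q-LES-Q-SF, preferring a luteal window is a choice of estimand and not the correction of an error.

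**What to change.** Keep the Day 1–2 administration and make three changes:

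1. At every SDS assessment, including baseline, and identically in both arms, instruct participants to rate the premenstrual (luteal) days of the cycle just ended. State in the instruction how those days are defined, since the documents give no number.
2. Change the SDS entry in Table 2 to that window.
3. Reword the objective in Section 2.1.2 to *functional impairment during the premenstrual (luteal) phase*.

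The cost is one instruction line on one form and two text edits, with no extra visit. The anchored window may differ from the instrument's usual reference period, so SDS scores become less comparable with outside norms. Using the same instruction in both arms and from baseline preserves the randomized comparison. For the Q-LES-Q-SF, the sponsor may keep the cycle-level window or adopt the same anchor; no correction is required.

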#### 2.1.3 Rationale for DRSP

The DRSP is a validated daily symptom diary designed to capture both physical and affective premenstrual symptoms according to DSM-5 criteria. Its prospective format minimizes recall bias and allows precise tracking of symptom fluctuations, making it appropriate for evaluating the efficacy of interventions in PMS.

## 3 Methods

### 3.1 Trial design

This study is a double-blind, placebo-controlled, randomized exploratory clinical trial designed to generate preliminary observations on feasibility, safety, and potential signals of *Brahmi* (Bacopa monnieri) tablets as an adjunct to Cognitive Behavioral Therapy (CBT) in managing Premenstrual Syndrome (PMS). Eligible participants will be randomly assigned to one of two groups: the trial group (CBT plus Brahmi) or the control group (CBT plus placebo). Randomization will be performed using a fixed block design with a block size of four to ensure balanced group sizes, with the sequence generated by a computer algorithm and maintained by a Medical Officer who is not involved in participant recruitment, intervention delivery, or outcome assessment. Both participants and study personnel involved in delivering CBT, assessing outcomes, and analyzing data will remain blinded to group assignments, ensuring methodological rigor and minimizing potential bias throughout the exploratory trial.

### 3.2 Study settings

The study will be conducted at Amrita Ayurveda Medical College Hospital, located in [name]. This institution is a constituent unit of Amrita Vishwa Vidyapeetham and serves as both a teaching and research hospital.

### 3.3 Eligibility criteria

Participants must give written, informed consent before participating in any study procedures.

#### 3.3.1 Inclusion criteria

Participants aged 18–24 years will be included to align with international youth definition while ensuring safety, methodological homogeneity, and minimizing confounding factors (26, 27).Regular menstruation with a menstrual interval of 25–35 days over the past 6 months.Participants scoring below 10 on the Patient Health Questionnaire-9 (PHQ-9) will be included, thereby excluding moderate to severe depression and ensuring the selection of individuals with PMS-related mood symptoms only.Diagnosed with moderate to severe PMS through PSST, the diagnosis will be confirmed with screening by the Daily Record of Severity of Problem (DRSP) scale for 2 menstrual cycles.

#### 3.3.2 Exclusion criteria

Known cases of Hypertension, Thyroid disorders, and Diabetes Mellitus. (Participants with hypertension (28), diabetes mellitus (29), or thyroid dysfunction (30) will be excluded to minimize confounding, as these conditions independently influence cardiovascular, metabolic, hormonal, and mood-regulating pathways that overlap with PMS pathophysiology).Under medication for any psychological or psychiatric disorders, substance use.Current PMS/PMDD treatment.Known case of pelvic pathology.Planning to conceive during the study period.Hormonal therapy.No access to mobile phones and the internet.

### 3.4 Interventions

The study intervention will span two menstrual cycles. Participants in the intervention group will receive one-to-one online Cognitive Behavioral Therapy (CBT) sessions, combined with a 500 mg *Brahmi* (Bacopa monnieri) tablet administered once daily after (31, 32) meals with lukewarm water. (33, 34) The control group will receive identical CBT sessions alongside a 500 mg placebo tablet containing inert excipients (dicalcium phosphate, talc, and starch), also taken once daily after food with lukewarm water. Oral medications will be withheld during the menstrual bleeding period for both groups.

The *Brahmi* and placebo tablets were procured from a GMP-certified manufacturer and underwent quality control and analysis to ensure safety, potency, and consistency. Both *Brahmi* and placebo tablets are film-coated to provide uniform appearance, stability, and ease of administration, with the placebo identical in color, shape, and packaging to maintain the double-blind design of the exploratory study.

Cognitive Behavioral Therapy (CBT) sessions will be conducted by two certified CBT therapists, both of whom hold a Master’s degree in Counseling Psychology and formal certification in CBT from accredited institutions. Each therapist has over 2 years of clinical experience in delivering CBT for stress- and mood-related disorders in outpatient settings.

Sessions will be delivered individually (one-on-one) to allow personalized assessment and guidance, ensuring that the intervention is tailored to each participant’s needs. In the event that one therapist is unavailable, the other will continue the intervention without disruption to maintain consistency.

A total of eight sessions will be delivered over two menstrual cycles, on the 5th, 12th, 19th, and 26th days of each cycle, with each session lasting approximately 45 min to 1 h. The CBT protocol is adapted from a previously published study on PMS and includes:

Protocol for Cognitive Behavioral Therapy sessions adapted from a standardized published study on CBT for PMS (7):

Following the previous study in Iran, a total of 8 sessions will be conducted. Except for 1*^st^* and last sessions, all sessions include both cognitive and behavioral aspects.**Session 1:** The general information on PMS/PMDD and its etiology are presented. While the last session included the instructions for the patients, such as the methods for relapse prevention. Both the cognitive and behavioral strategies were discussed in sessions 2 to 7.**Session 2:** Psychological training on the role of thoughts and their relationship with emotions and behavior (cognitive triangle) and psychological training on the relationship between stress and PMS and teaching relaxation techniques.**Session 3:** Changing the topic to PMS and psychological training on the interdependence between nutrition, exercise, and PMS.**Session 4:** Reconstruction of dysfunctional perceptions and How to integrate exercise into daily life using a motivational program and strategy.**Session 5:** Psychological training on certain superstitions about PMS and applying the cognitive strategies learned and what is a balanced diet and how to follow it in daily life.**Session 6:** Psychological training on effective thoughts and developing new assessments and Psychological training on the impact of stress-related errors on reasoning.**Session 7:** Certain behaviors to improve PMS (use of healthcare, seeking support, and communication) and Training on participating in positive activities in daily life.**Session 8:** Instructions for the participants such as the methods of relapse prevention.

